### *Data formatting*

The data are split longitudinally from a patient's entry date to their exit or censor date using time-intervals defined by screening episodes. If a patient has had 5 screening episodes after entry (so s1 s2 then 5 after that) this would mean that they have 5 rows in the dataset. Covariates get updated at each screening episode.

### *Event dates*

The date of the event will be taken as the date of screening on which referable retinopathy was detected. Each person time interval has a binary flag for whether an event occurred in a person-time interval.

We also have a censor date (which is the earliest of death/event/study end date/end of observability). If a person is censored and his event flag is 1, then that means he was censored because of the event. If at the person's last time-interval the event flag is 0, then he was censored for one of the other reasons (i.e. akin to a SURV object in R for Cox regression).

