## **Inclusion criteria, entry and exit times**

The study will focus on the diabetes population aged 12 years and upwards since this is the group eligible for screening in national policy.

*Type 1 diabetes* : is defined by an algorithm that starts with the clinical assignment of type 1 in the clinical record but then excludes anyone with evidence of type 2 based on extensive oral prescription drug use or more than a year from diagnosis to insulin.

Type 2 diabetes: is defined by the clinical assignment of type 2 unless there is evidence to contradict this.

*Date of diagnosis*: this is taken from SCI-DM – in a small % of cases date of diagnosis is not known and earliest date known to have diabetes has to be used instead.

*Study start date*: 01/01/2007

*Study end date*: 01/06/2016

*Patient entry date* is defined as the latest of study start date, the date of diabetes diagnosis, and the date first evaluable for events (as defined below). Note that for the modelling purposes patient entry date will be further refined to be S2 day +1.

*Patient exit date* for a patient is the earliest of

- i) study end date,
- ii) the date of death,
- iii) the date last evaluable for events (as defined below)
- iv) or the date of the first event of interest.

Those who exit before an event or study end date are considered to be censored.

*Date first evaluable for events*

The dates from which individual patients are first considered evaluable for events are estimated from the dates of when either clinical measures (BMI, HbA1C and blood pressure [BP]) or drug prescription data are first available for that person, since these records confirm that a patient was in Scotland at the time and can therefore be considered evaluable for events.

*Date last evaluable for events*

The date last observable for events is defined as the earliest of

- i) the date last observable for routine data or drug data (i.e. exit from the country) whilst not under admission to hospital plus an additional 183 days
- ii) death, or 01/06/2016; Sensitivity analyses will evaluate the impact of this 183 day period which is in place so as not to censor people too early who simply haven't had any contact with clinical services during the period but who are still under observation.
- iii) *Date of suspension from screening for non eye disease related reason. Such patients can re-enter once the suspension has been lifted as evidenced by a further screening event*

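### Events can be recorded only at a screening, yet the exit and censor rules keep event-free patients at risk beyond their last one; this contradicts the five-row example and, if followed, understates absolute predicted risk

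*SAP*

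**What the plan says.** Under Event dates, the SAP ties events to screenings: "The date of the event will be taken as the date of screening on which referable retinopathy was detected". The same section sets the end of follow-up: "We also have a censor date (which is the earliest of death/event/study end date/end of observability". It adds that a zero flag on a person's last interval means censoring for a reason other than the event.

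Under Inclusion criteria, entry and exit times, the end of observability depends on routine or drug data, "whilst not under admission to hospital plus an additional 183 days", or on "Date of suspension from screening for non eye disease related reason". The general entry date "is defined as the latest of study start date, the date of diabetes diagnosis, and the date first evaluable for events", so it is not tied to a screening. The models use another entry: "Note that for the modelling purposes patient entry date will be further refined to be S2 day +1". One safeguard is planned: "Sensitivity analyses will evaluate the impact of this 183 day period".

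Under Data formatting, the first sentence splits the data up to the exit or censor date, with cut points at the screenings. The example then says that a patient with "5 screening episodes after entry (so s1 s2 then 5 after that) this would mean that they have 5 rows". Under Poisson regression, each row enters with the log of its length as an offset.

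**The concern.** A row that runs from the last screening to death, study end or last contact plus 183 days adds exposure but can never carry an event. The clock for the models starts just after a screening, so there is no matching unobserved stretch at the start to balance it. The fitted baseline rate therefore falls.

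This matters because the output is used on the absolute scale: Utility assessment sets screening intervals by risk thresholds such as 1%, 2.5% and 3%. A risk that is understated leads to a longer interval. Patients who stop attending but still have prescriptions or clinic measurements carry the longest such stretches, since those records alone keep them under observation.

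The text also contradicts itself, so two programmers could build different datasets from it.

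**Working it through.** **Row count (the plan's own figure).** Call the screenings S1 to S7, with entry the day after S2. The intervals S2–S3, S3–S4, S4–S5, S5–S6 and S6–S7 make 5 rows, as the SAP states. An event-free patient with a censor date after S7 has one more, S7 to censoring, which makes 6. The example does not give the patient's event status. If the event is found at S7, both rules give 5, but the row count is stated as general. For an event-free patient it fits only if rows stop at the last screening.

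**Simple size check.** With K yearly screenings after entry and an unobservable tail of T years, the relative error in the rate is about K/(K+T) − 1. With annual screening the tail averages about 0.5 year:

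- K = 1: 1/1.5 − 1 = −33%
- K = 3: 3/3.5 − 1 = −14%
- K = 5: 5/5.5 − 1 = −9%
- K = 8: 8/8.5 − 1 = −6%

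**Simulation.** From the SAP: study window 01/01/2007 to 01/06/2016 (9.42 years), annual screening, 183 days (0.50 year), model entry just after S2. Assumed, because the SAP gives no figures: constant onset rate, no grading error, death 3% and leaving 1.5% per year, last contact up to 0.5 year before leaving, and entry either at the window start or staggered. The estimate is events divided by person-years. The target is (1 − exp(−rate × interval))/interval; at 2.5% per year and annual screening it is 1 − exp(−0.025) = 0.0247.

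| Attendance, entry pattern | To the stated censor date | To the last screening |
|---|---|---|
| Full, window start | 0.0231 (−7%) | 0.0247 |
| Full, staggered | 0.0220 (−11%) | 0.0250 |
| 3%/yr stop attending, window start | 0.0202 (−18%) | 0.0248 |
| 3%/yr stop attending, staggered | 0.0197 (−20%) | 0.0245 |
| 5%/yr stop attending, window start | 0.0184 (−26%) | 0.0245 |
| 5%/yr stop attending, staggered | 0.0183 (−26%) | 0.0243 |

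Repeat runs differ by a point or two. With full attendance and onset of 1–5% per year, the shortfall is 5–12% with annual screening and 13–28% with an assumed two-year interval.

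**What it does to a threshold.** If predicted risk is 10% too low, a patient shown 2.5% has 2.5/0.90 = 2.8%. If it is 25% too low, 2.5/0.75 = 3.3%.

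**Would the plan notice?** Removing the 183 days changes 0.0231 to 0.0232 and 0.0220 to 0.0222, so that sensitivity analysis barely moves the result. Most of the tail runs from the last screening to study end or death. The 30% test set is built by the same rules, so predicted and observed rates there share the error and calibration would look sound.

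**Objective 1 rates.** Here entry is not tied to a screening. With full attendance and annual screening, keeping the tail gives −1% to +2%, because the short stretch before the first screening offsets it. With 3–5% per year stopping attendance, the rates are about 7–19% too low at 2.5% onset. Ending at the last screening while leaving entry as it is overstates them by about 6–15%.

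**The case against.** The strongest reply is that the only worked example leaves the tail out, so the authors may intend the right dataset. That is a fair reading of intent, and it is why the bias is conditional. But the exit definition, the first sentence under Data formatting and the censor date under Event dates all point the other way. An example does not override three stated rules.

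A second reply is that interval censoring is not ignored: Poisson regression mentions a different link, and non-parametric interval-censored methods and hidden Markov models are also planned. Such a likelihood could remove the problem. However, the link is only something that may be used, the non-parametric methods are only to be evaluated, and the hidden Markov score is fed into the fuller covariate model.

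Third, the larger shortfalls rest on assumed non-attendance. That stands: the SAP gives no attendance figures, and patients formally suspended for non-eye reasons are censored.

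A reader might also infer more than the document supports:

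- *Every regression coefficient is biased low.* It is not. A tail that takes the same share of time in all patients moves the intercept only. Slopes change for covariates related to attendance, and in either direction.
- *The observed rates of objective 1 are biased low.* This is not shown under full attendance, since the S2 entry is stated for modelling only.
- *One row in six of the plan's example can hold no event.* The example has five rows; the sixth exists only under the other rule.
- *Eye-related suspension leaves many patients wrongly at risk.* Follow-up already ends at a first referable event, and the SAP does not say how many such suspensions come before one.

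**Conclusion.** The SAP contains a real contradiction about where modelling person-time ends, and the rule it states most often gives a wrong result. If the exit and censor dates are applied as written, the baseline rate and absolute predicted risks are too low: by roughly 5–12% with annual screening and full attendance, and by about a fifth to a quarter if 3–5% per year stop attending but remain in contact. The direction follows from entry just after a screening combined with a tail in which nothing can be detected. The size depends on assumed onset, attendance, death and leaving rates. If the five-row example governs, the tail does not enter the models and this bias does not arise. Neither planned safeguard would tell the two datasets apart.

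**What to change.** Under Inclusion criteria, Data formatting and Event dates, state that modelling person-time for a patient without an event ends at the last screening on or before the current exit date. This agrees with the five-row example. Alternatively, name an interval-censored likelihood as the primary model instead of an option. Keep the current exit date as a sensitivity analysis.

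For objective 1, define entry and exit separately and change them together: start at a screening without referable disease and end at the last screening. Changing exit alone would replace one error with another.

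The cost is small: a wording change and a short edit to data preparation. No model events are lost, because each is dated to a screening. Some person-time goes, patients with no screening after S2 contribute no rows, and objective 1 is limited to patients with an earlier screening free of referable disease. Ending at the last screening also assumes that, given the covariates, those who stop attending have the same risk as those who continue; the SAP should say so.

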### **Initial tabulations**

For each continuous covariate being considered :

- Summarise its distribution as mean median sd iqr and range and plot its distribution (density or histogram) plot
- Tabulate the frequency of all categorical variables

Events:

- Show the number (%) and event rate of incident events during follow up By AGE and SEX and diabetes type
- By Sex strata and for broad age bands and all ages combined show the age standardised event rate for each of the event of interest standardised to the 2013 European Standard Population

Then with any referable retinopathy as the event of interest :

- Summarise the distribution of follow up time range of person entry and exit dates
- Summarise the distribution of covariates at baseline by subsequent event status

- In the same table show the p value and the beta regression coefficient for the current age - sex -and diabetes duration -adjusted associations of all variables with the outcome

## Model construction

*Assuming any referable retinopathy as event of interest initially:*

### a. Poisson regression

We will use Poisson regression model with backward elimination but we may use a different link function to deal with the interval censoring - In addition we will evaluate the use of non-parametric methods for interval-censored survival analysis in place of the interval regression models.

All model fitting will be done on 70% of the data (selected randomly by patient, maintaining ratio of events), and the remaining 30% will be used for internal validation. We will randomly assign the individuals in the dataset into these two partitions.

We include current age, sex, and diabetes duration as our base set of covariates in our initial model and will then use backward elimination to drop variables from the model, using a reduction in AIC of  $< 2$  units as the selection/stopping criterion.

We will initially include a simple covariate of screening status at last screening as a covariate

We will then extend this to be a weighted score of all prior screenings weighted by how recent the measure is

The model will contain an offset term for the  $\log(\text{length of interval})$ .

We will also select across age and sex interaction terms for each covariate.

To be agreed : should we include any shrinkage/ penalizing?

*Assumption about linearity of effects of covariates :*

We will use backward elimination with multivariable fractional polynomials

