### Utility assessment

To be expanded: We will compare the estimated number of screenings required to maintain interval disease rate below a given threshold using the maximally predictive model from the above process with a much simpler decision algorithm such as i) the current annual screening for all programme and ii) a programme that would screen all type 1s annually and all types 2s biannually.

Since there are many ways in which policy formulations might utilise prediction risk. We will produce some examples; for instance we can show what the impact on number of screens per annum based on individualised screening intervals set by a series of thresholds of risk (e.g. 1% or 2.5% or 3%). We can also calculate the number of people who will potentially have a delay of >3 months in detection of referable disease and calculate the median 'delay' for each scenario (i.e. the interval between when they would have been screened based on current screening scheme and when they would be screened under the new scheme). The aim is that the models will be able to evaluate a wide range of potential screening policies to provide interactive feedback to policy makers.

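### The default Poisson model with a log-length offset, fitted to a yes/no flag per screening interval, gives rates that depend on interval length; the correcting link is optional and unnamed

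*SAP*

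**What the plan says.** Four statements in the SAP combine to define the main model.

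- *Data formatting*: follow-up is split "using time-intervals defined by screening episodes", with one row per screening interval.
- *Event dates*: "Each person time interval has a binary flag for whether an event occurred in a person-time interval", and "The date of the event will be taken as the date of screening on which referable retinopathy was detected". A case row therefore ends at the detecting screen, not at onset.
- *a. Poisson regression*, on the choice of model: "We will use Poisson regression model with backward elimination but we may use a different link function to deal with the interval censoring". The same section adds: "The model will contain an offset term for the" log of the interval length.
- *a. Poisson regression*, on alternatives: "In addition we will evaluate the use of non-parametric methods for interval-censored survival analysis in place of the interval regression models".

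The two-step approach in section b feeds the hidden Markov risk score into this same covariate model. Objective 4 and *Utility assessment* then use the best-predicting model to set individual intervals from risk thresholds (1%, 2.5% and 3% are the examples). They compare the result with annual screening for all and with "a programme that would screen all type 1s annually and all types 2s biannually".

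**The concern.** A Poisson log-link model with a log-length offset sets the expected response equal to rate times length. The response here is 0 or 1, and onset is known only to lie somewhere within the row. Under a constant hazard, the probability of a flag is 1-exp(-hL), which flattens as hL grows, while the Poisson mean keeps rising in proportion to L. In effect a case is credited with its whole interval as time at risk.

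The fitted rate is therefore not a property of the patient alone. It depends on how far apart the screens happened to be, and contrasts between low-risk and high-risk patients are compressed. A tool that chooses a different interval needs a rate that can be carried from one length to another. The AIC used for backward elimination would also come from a likelihood that does not fit binary rows: at a mean of 0.30 the Poisson variance is 0.30, against 0.30 x 0.70 = 0.21 for a 0/1 flag.

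**Working it through.** The SAP states no event rate, so there is no figure of its own to reproduce. The risks per interval below are assumptions, shown as a range. The hazard is taken as constant within an interval, and screening is taken to detect what is present.

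**1. Error in the hazard.** Let p = 1-exp(-hL) be the risk over one interval. The true cumulative hazard is hL = -ln(1-p). The log-link Poisson fit targets p/L, so fitted/true = p / (-ln(1-p)).

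| Risk per interval | -ln(1-p) | Fitted/true | Understatement |
|---|---|---|---|
| 1% | 0.0101 | 0.995 | 0.5% |
| 2.5% | 0.0253 | 0.987 | 1.3% |
| 3% | 0.0305 | 0.985 | 1.5% |
| 10% | 0.1054 | 0.949 | 5.1% |
| 20% | 0.2231 | 0.896 | 10.4% |
| 30% | 0.3567 | 0.841 | 15.9% |

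**2. Dependence on interval length.** Take h = 0.3567 per year (30% one-year risk).

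- If all rows last one year, the Poisson rate is 0.300.
- With equal numbers of 0.5-, 1- and 2-year rows, the risks are 0.163, 0.300 and 0.510. The pooled rate is (0.163 + 0.300 + 0.510)/(0.5 + 1 + 2) = 0.973/3.5 = 0.278.

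The same patients yield a different rate because the screening schedule differs.

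**3. Simulation.** In 300,000 rows, with two groups at hazards 0.01 and 0.3567 (true ratio 35.7), three interval patterns were tried: all one year; one year for low risk with six months for high risk; and a mix of 0.5, 1 and 2 years.

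- Poisson log link: high-risk hazard 0.302, 0.329 and 0.279; hazard ratio 28.6 to 33.4.
- Binomial complementary log-log with the same offset: high-risk hazard 0.359 in all three patterns; hazard ratio 35.4 to 36.5.
- The low-risk hazard was essentially unaffected under either model.

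**4. Carrying risk to another length.** Fit on one-year rows and predict two years. The true risk is 1-(1-p)^2. The Poisson rate can be converted as 1-exp(-2p), or its mean 2p can be used directly.

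| One-year risk | True two-year risk | 1-exp(-2p) | Mean 2p |
|---|---|---|---|
| 3% | 5.91% | 5.82% | 6.00% |
| 10% | 19.0% | 18.1% | 20.0% |
| 30% | 51.0% | 45.1% | 60.0% |

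**5. Interval at which risk reaches 3%.** The true interval is -ln(0.97)/h. For a one-year risk of 30% it is 0.0305/0.3567 = 0.085 years, against 0.100 to 0.102 years under Poisson (about 31 days against 37). For a one-year risk of 1% it is 3.03 years, against 3.00 to 3.05.

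**6. Would the planned validation show it?** *Performance evaluation* uses a random 30% of patients, whose interval lengths follow the same distribution as the fitting data. If all rows have one length, the Poisson mean is right at that length. If lengths are mixed, it is right on average over them but not at each one. Calibration on such a sample would not fully reveal an error that appears at other lengths.

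**The case against.** The SAP is not blind to the problem. The sentence that names Poisson also names interval censoring and keeps a different link in reserve, and non-parametric interval-censored methods are to be evaluated. A reader might infer that the authors overlooked the issue; the text does not support that. What stands is that the remedy is only permitted, no link is named, and nothing says when to switch.

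A reader might also infer that the Poisson family must be abandoned to remove the bias. That is too strong. The fault lies in the mean function. A Poisson likelihood with a complementary log-log mean gave a hazard of 0.362 in a mixed-interval simulation, identical to the binomial fit, against 0.281 with the log link. The binomial family is preferable because the rows are binary and AIC should come from their own likelihood.

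Nor can one say that high-risk patients will be given risks that are too low. The sign depends on the rate-to-risk conversion: 45% or 60% against 51% in the example above.

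Finally, the practical effect may be small. At the SAP's example thresholds the hazard error is at most about 1.5%. The 30% case moves the interval by about 6 days, while the SAP's own delay example is more than three months. AUROC, which the SAP regards as its most valid metric, depends on ranks and should change little. All of this stands, and it limits the size of the point. It does not answer the two-year comparison, where a changed interval is applied to patients at every level of risk.

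**Conclusion.** The point holds as a flaw in the stated default, with a remedy left open. Fitted as written, the model returns rates below the true hazard that depend on the observed interval lengths and do not transfer cleanly to the intervals that Objective 4 and *Utility assessment* must evaluate. The hidden Markov two-step model inherits the same problem.

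The size is negligible to small at 1% to 3% risk per interval, passes 5% of the hazard at about 10% risk, and is about 16% at 30% risk. How many patients lie in the upper range cannot be told from the SAP, so no overall effect on screening numbers can be claimed. The figures assume a constant hazard within intervals. The change is worth making because it costs almost nothing and settles the primary likelihood before the data are analysed.

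**What to change.** In section a, replace the optional wording with a commitment, for example: the event flag of each row will be analysed by binomial regression with a complementary log-log link and an offset equal to the log of the interval length; risk over any interval t will be computed as 1-exp(-exp(linear predictor) x t), the linear predictor being taken without the offset. State that this likelihood is also used for AIC, backward elimination and fractional polynomial selection, and that the hidden Markov score enters this model. Keep the non-parametric interval-censored methods as the comparison already planned.

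The cost is a sentence or two in the SAP and a changed family and link in the model call. No further data are needed.

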**13.01.17**

## **Aims**

We aim to develop risk prediction tools that can be used by retinopathy screening services to define the optimal interval to next screening in the national screening programme taking into consideration past screening records and other covariates available in SCI-DM

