## **Objectives**

To further this aim we will

- 1) first calculate the currently observed age and sex and diabetes type specific rates of first referable retinopathy in the screening programme and describe these by calendar year
- 2) Build a predictive model and validate its prediction performance of time to first referable disease
- 3) Extend that model to utilise a hidden markov model derived measure of risk and assess whether this improves predictive performance
- 4) compare the estimated number of screenings required to maintain interval disease rate below a given threshold using the maximally predictive model from this process with a much simpler decision algorithm such as the current programme and a programme that would screen all type 1s annually and all types 2s biannually.

The models will be developed for type 1 and type 2 separately

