### b. Two-step analysis with multi-state modelling & survival analysis:

We will use hidden Markov models to model the DRS data. The advantages to this approach are that it allows us to model the risk for transition incorporating all available data on prior screening even though individuals have variable number of examinations at differing intervals. It also allows us to model grading misclassification as it separates the 'true but unseen grade' from the 'observed grade'. We will fit separate models by diabetes type and the models will be adjusted for age, sex and diabetes duration. As it is not feasible to extend the multi-state modelling approach to a more complex model that includes many clinical covariates we will "plug in" the risk score computed from the hidden Markov model into the fuller model that includes all available clinical covariates as described above.

**One-step survival analysis:** We will evaluate an alternative approach of not using the hidden Markov model but instead fitting separate models for individuals with 0, 1, 2 or more previous examinations. This is possible as we have a large dataset so that we will have an adequate sample size to learn a predictive model within each of these strata.

**Non-parametric methods:** We shall also evaluate non-parametric methods for interval-censored survival analysis. These kernel-based methods, which make predictions based on a function that evaluates the similarity between pairs of observations, generally outperform simple regression models for prediction though the predictions are not readily explainable.

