### Performance evaluation

The performance of the final model will then be reported from the test dataset.

Discrimination will be assessed using a C-statistic (area under the receiver operating characteristic [AUROC]). We will calculate the AUROC within age and sex strata and then take a weighted average of these to define the final AUROC.

Calibration will be summarized using a calibration plot, calibration slope, and Hosmer-Lemeshow test.

We will also report out the net reclassification indices and the IDI. However note that we consider the AUROC to be the most valid of these. Integrated Discrimination Index (IDI). The IDI =  $(IS_{new} - IS_{old}) - (IP_{new} - IP_{old})$  where IS is the integral of the sensitivity across all possible cut-off values for the new ( $IS_{new}$ ) and old models ( $IS_{old}$ ) and IP the corresponding integral of 1-specificity with the new model reflecting the model with added clinical covariates and the old model being based only on the DRS screening data. These metrics will allow us to assess how well these models improve prediction of risk for transition to referable eye disease.

In the test set we will compare the predictive performance of the prediction model with this hidden markov derived measure with the simpler indices of past screening results as described under a. above

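### All model fitting stays on a random 70% of patients and no re-estimation is planned, so the final coefficients lose some precision that a cheap refit would recover

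*SAP*

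**What the plan says.** Subsection a (Poisson regression) of Model construction sets the rule: "All model fitting will be done on 70% of the data". The partition is made at patient level with the event proportion preserved ("selected randomly by patient, maintaining ratio of events"), and "the remaining 30% will be used for internal validation". Performance evaluation continues: "The performance of the final model will then be reported from the test dataset". Utility assessment then takes the best-predicting model from that process into the comparison of screening policies, without naming a partition or a coefficient set.

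The purpose under Aims is a tool to "define the optimal interval to next screening in the national screening programme". Objectives adds that "The models will be developed for type 1 and type 2 separately". Subsection b considers, as an alternative approach, separate models by number of previous examinations, and expects an "adequate sample size to learn a predictive model within each of these strata" on the ground that the dataset is large. The SAP gives no patient or event count.

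No section mentions re-estimating the selected model on all patients after the test-set evaluation, and none says which coefficients would be released.

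**The concern.** The held-out 30% has a proper job. Variables, fractional polynomials and interactions are all selected from the data, so an untouched test set is needed for an honest estimate of discrimination and calibration. That job ends once performance has been reported. After that, the held-out events can sharpen the coefficients without harming the validation, but the plan as worded stops at the 70% fit.

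The coefficients are the product here, because screening services would use them to set individual intervals. Utility assessment gives example risk thresholds of 1%, 2.5% and 3%, so imprecision in an individual's predicted risk passes into the interval assigned. The data are also subdivided by diabetes type and, in one alternative approach, by number of previous examinations. Age and sex interactions are considered for every covariate, and the question of shrinkage is left open. A model with few events has the least precision to spare.

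**Working it through.** **Inputs from the SAP**
- Fraction used for fitting: 0.7; fraction held out: 0.3 (Model construction, subsection a).
- The event proportion is kept in the split, so about 70% of events inform the coefficients and about 30% fall in the test set.
- The SAP states no event count, sample size or precision target, so there is no figure of its own to reproduce.

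**Relative loss (any event count, fixed specification)**

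In a Poisson model the information is proportional to the number of events.
- Variance ratio, 70% fit to full fit: 1/0.7 = 1.43.
- Standard error ratio: 1/sqrt(0.7) = 1.195, that is, 19.5% larger.
- Gain from refitting on all patients: 1 − sqrt(0.7) = 1 − 0.837 = 0.163, that is, standard errors 16.3% smaller.

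**Absolute loss (event count assumed)**

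The standard error of a log rate ratio per standard deviation of a covariate is taken as about 1/sqrt(events). The 95% confidence factor, by which the rate ratio is multiplied or divided, is exp(1.96 × SE). For example, with 500 events in total:
- 70% fit: 350 events, SE = 1/sqrt(350) = 0.0535, factor exp(1.96 × 0.0535) = 1.110.
- Full fit: 500 events, SE = 1/sqrt(500) = 0.0447, factor exp(1.96 × 0.0447) = 1.092.

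| Total events in the model (assumed) | Events in the 70% | Factor, 70% fit | Factor, full fit |
|---|---|---|---|
| 500 | 350 | 1.110 | 1.092 |
| 2,000 | 1,400 | 1.054 | 1.045 |
| 10,000 | 7,000 | 1.024 | 1.020 |
| 20,000 | 14,000 | 1.017 | 1.014 |

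The ratio of standard errors is the same in every row. The difference between the two factors shrinks from 0.018 at 500 events to 0.003 at 20,000.

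The calculation covers the precision of the estimated coefficients only. A refit with the same terms does not undo the fact that those terms were chosen on 70% of patients.

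**The case against.** Reporting performance on a held-out set requires a 70% fit, so the sentence in subsection a may do no more than describe the development and validation split. Releasing exactly the model that was tested is also a legitimate choice, because the reported calibration and discrimination then belong to the released coefficients. And the data come from a national database of patients with a diabetes code, over a study period from 2007 to 2016, which the plan itself calls large: "This is possible as we have a large dataset so that we will have an adequate sample size".

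Much of this stands. A reader might infer that the national tool is bound to carry the 70% coefficients. The SAP does not say which coefficients are deployed; the inference rests on the word all, on the term final model, and on silence about a refit. A reader might also infer that 30% of the events are ignored. They are not: they serve the validation and are absent only from the coefficients. Nor is there any bias, since the split is random by patient. Finally, the loss is probably small in absolute terms if events run to many thousands.

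What does not stand is that the matter can be left alone. The claim of adequate size in the strata comes without a number. The benefit of releasing the tested set has to be weighed against a known loss of precision that one further run per model would remove, and the plan does not make that choice openly.

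**Conclusion.** The point holds as a cheap improvement, not as an error in the validation design. Followed as written, the final coefficients use about 70% of the events, with standard errors 19.5% larger than a fit to all patients would give under the same specification. That ratio rests on information proportional to events and on the event proportion being kept in the split.

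The practical size cannot be settled from the SAP. Over the assumed range of 500 to 20,000 events per model it runs from noticeable to negligible. If it matters anywhere, it is in models with few events. Type 1 models, strata by number of previous examinations and the secondary endpoints, if modelled, are candidates, but the SAP gives no counts to show that any of them is sparse.

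**What to change.** Add to Model construction (subsection a) and Performance evaluation:
- Once test-set performance is final, the selected specification, with the same terms and transformations and no new selection, is re-estimated on 100% of patients, separately by diabetes type. Those coefficients are published as the tool.
- The reported discrimination and calibration belong to the 70% fit.

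Add to Utility assessment that the numbers of screens and the delays are computed with the 70% fit in the held-out 30%. If the refitted coefficients were used there, those patients would no longer be out-of-sample and the utility results could be optimistic.

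The cost is a few sentences and one extra run per model. The downside is that the published coefficients differ slightly from the set that was tested, which should be stated alongside them.
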